**Fig. 4 Fig4:**
[figure not shown]
Treatment. **a** Rapid intermittent correction with hypertonic saline in patients with moderately severe or severe symptomatic hyponatremia. *min* minute, *Na* sodium, *bwt* body weight. ↑, increase. **b** Slow continuous correction with hypertonic saline in patients with moderately severe or severe symptomatic hyponatremia. *hr* hour, *Na* sodium, *bwt* body weight. ↑, increase; Δ, delta – change in amount

### From 24 to 48 hours

In both moderately severe and severe cases of hyponatremia, repeated infusion of 2 mL/kg 3% hypertonic saline over 20 min at every sample time point (at 30, 36, 42, and 48 h) is recommended until the sNa level increases to 10–17 mmol/L from the initial sNa or until the sNa reaches 130 mmol/L, and until the symptoms improve.

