### Study design

This study is a prospective, investigator-initiated, multicenter, open-label, randomized controlled study with two experimental therapy groups. We have followed the Standard Protocol Items: Recommendations for Interventional Trials (SPIRIT) 2013 Statement which defines standard protocol items for clinical trials [24] (see Additional file 1). The study algorithm is depicted in Fig. 1 and the SPIRIT and study schedule are given in Figs. 2 and 3. After enrollment, clinical follow-up will be performed 2 days after treatment with 3% hypertonic saline.

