### Physician’s practical treatment guidelines according to the sNa level

The principal purpose of this study will be to compare the rapid intermittent correction group to the slow continuous correction group [29]. According to a review of the medical literature on the treatment of hyponatremia, treatment with hypertonic (3%) saline is recommended in cases of severe symptomatic hyponatremia [1, 15, 16]. Therefore, the rate of infusion of 3% saline will be stratified based on the symptom severity in each group. After randomization, the participants will undergo either rapid intermittent correction or slow continuous correction of hyponatremia for 48 h. Treatment in the intermittent bolus group will comply with European guidelines published in 2014, and the slow continuous infusion will be guided by widely accepted methods [1, 13–16]. The treatment goals are to raise the sNa level by 5–9 mmol/L from the initial sNa and to achieve symptom relief within the first 24 h, and to raise the sNa level by 10–17 mmol/L from the initial sNa or ≤130 mmol/L, and to achieve symptom relief during the 48 h [10–12]. We will also check for overcorrection at every sample time point and conduct relowering treatment. Relowering treatment is performed as below if the achieved sNa level is ≥10 mmol/L at any sample time point within the first 24 h or the achieved sNa level is ≥18 mmol/L at any sample time point within 48 h [1, 13–16]. The treatment goal, relowering treatment strategy, and cause-specific treatment of hyponatremia will be applied to each group equally.

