### From 24 to 48 hours

The infusion protocol will be modified as below according to the sNa levels at every sample time point (at 30, 36, 42, and 48 h). If the Na level increases to 10–17 mmol/L above the initial sNa level or sNa reaches 130 mmol/L, and symptom relief is observed, the 3% hypertonic saline infusion should be discontinued regardless of changes in the sNa level during the previous 6 h. If the Na level increase is less than 1.5 mmol/6 h, it is recommended to add 3% hypertonic saline infusion at a rate of 0.25 mL/kg/h to the previous infusion rate or to restart the infusion at a rate of 0.25 mL/kg/h if it was previously discontinued. If sNa levels increase at a rate of over 1.5 mmol/6 h, the 3% saline infusion rate should be maintained.

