### Clinical and laboratory evaluations

The physical examination, laboratory evaluations, and medication reviews will be conducted before treatment; the laboratory evaluations will include a complete blood count, serum electrolytes, blood urea nitrogen, creatinine, calcium, phosphorous, protein, albumin, and glucose; a liver function test; a thyroid function test (TFT); rapid adrenocorticotropic hormone (ACTH) test (basal cortisol, ACTH, cortisol at 30 min and 60 min), serum osmolality; urinalysis, urine electrolytes, urine osmolality. sNa levels will be measured every 6 h for 2 days [30]. The GCS score will be assessed before treatment and at 24 and 48 h of treatment. All types and volumes of administered fluid during 48 h will be monitored.

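### The treatment rules direct 3% saline decisions at 48 h, when protocol treatment, sodium sampling and the relowering check all end; these sections must be reconciled

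*Protocol article*

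**What the plan says.** All references are to the protocol article.

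- **Rapid intermittent bolus group, From 24 to 48 hours:** "repeated infusion of 2 mL/kg 3% hypertonic saline over 20 min at every sample time point (at 30, 36, 42, and 48 h"), until the sodium goal is met and symptoms improve. The last listed bolus point is 48 h.
- **Slow continuous correction group, From 24 to 48 hours:** the infusion is modified "according to the sNa levels at every sample time point (at 30, 36, 42, and 48 h"). It stops only when the sodium goal and symptom relief are both present. If the rise is too small, the instruction is to "add 3% hypertonic saline infusion at a rate of 0.25 mL/kg/h to the previous infusion rate" or to restart a stopped infusion at 0.25 mL/kg/h. If the rise is adequate, "the 3% saline infusion rate should be maintained". All these options apply at 48 h.
- **Physician's practical treatment guidelines according to the sNa level:** "the participants will undergo either rapid intermittent correction or slow continuous correction of hyponatremia for 48 h".
- **Clinical and laboratory evaluations:** "sNa levels will be measured every 6 h for 2 days". Administered fluids are monitored during 48 h.
- **Physician's practical treatment guidelines and Safety issues:** overcorrection is checked at each sample time point. Relowering is triggered by a rise of at least 10 mmol/L at a sample within 24 h, or at least 18 mmol/L at a sample within 48 h.
- **Study design:** "clinical follow-up will be performed 2 days after treatment with 3% hypertonic saline". No sodium test is named there.
- **Outcome measures:** the primary outcome is a rise above 12 mmol/L within 24 h or above 18 mmol/L within 48 h.

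**The concern.** The 48-h time point has two incompatible roles. In the arm-specific rules it is a decision point at which more hypertonic saline may be given. In the sections on treatment duration, sampling, fluid recording and relowering it is the end.

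A patient who is not at goal at 48 h, or who is at goal without symptom relief, would under the arm rules receive 3% saline after the last protocol sodium. No protocol check would follow that could trigger relowering. Sites could also differ in practice: one may stop the slow infusion because correction lasts 48 h, while another continues it because the slow-arm rule says so. The Discussion already expects protocol violations because physicians and nurses work in shifts.

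What is at stake is the safety monitoring of these patients and uniform conduct, in a trial whose subject is the safety of sodium correction.

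**Working it through.** **1. The plan's own figure.** The only calculated figure is the sample size. With 20% versus 5%, two-sided 5% and 80% power, the pooled-variance formula without continuity correction gives 75.12 per group. Allowing for 15% dropout, 75.12 / 0.85 = 88.4, which rounds up to the stated 89. Nothing below depends on it.

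**2. Schedule check.**

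| Saline decision (h) | Next protocol sodium (h) |
|---|---|
| 0 | 1 |
| 1 | 6 |
| 6, 12, 18 | 12, 18, 24 |
| 24 | 30 |
| 30, 36, 42 | 36, 42, 48 |
| 48 | none described |

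The pattern is the same in both arms. Every saline decision except the one at 48 h is followed by a sample, and so by an overcorrection check.

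**3. Does the slow infusion end at 48 h?** The general treatment section says that correction lasts 48 h. The slow-arm section lists maintaining, increasing or restarting the infusion at 48 h. If treatment ends at 48 h, those instructions have no effect there. If they do have effect, treatment does not end at 48 h. The text does not settle which.

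**4. Possible size of the unmeasured rise.** The article gives no model, so the following are assumptions: 3% saline at 513 mmol/L, body water W of 0.45–0.60 L/kg, and no urine loss. Current sodium is taken as 110–136 mmol/L, which is an assumed starting value of 110–120 plus a rise of up to 16. For a volume v in L/kg:

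rise = (513 − sNa) × v / (W + v)

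| Saline | v (L/kg) | Low: sNa 136, W 0.60 | High: sNa 110, W 0.45 |
|---|---|---|---|
| Bolus, 2 mL/kg | 0.0020 | 377 × 0.0020 / 0.6020 = 1.25 | 403 × 0.0020 / 0.4520 = 1.78 |
| 0.25 mL/kg/h for 6 h | 0.0015 | 377 × 0.0015 / 0.6015 = 0.94 | 403 × 0.0015 / 0.4515 = 1.34 |
| 0.5 mL/kg/h for 6 h | 0.0030 | 377 × 0.0030 / 0.6030 = 1.88 | 403 × 0.0030 / 0.4530 = 2.67 |

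The infusion rows apply only if the infusion is read as continuing past 48 h. The 6 h is the protocol's sampling interval, used for illustration. Higher rates scale almost in proportion, but the article does not say what rates would be running at 48 h.

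**5. Patients near the limit.** Starting values of 110–120 put a patient at +16 at a sodium of 126–136, and a patient at +17 at 127–137. The same formula then gives:

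| At 48 h | After 2 mL/kg bolus | After 6 h at 0.25 mL/kg/h | After 6 h at 0.5 mL/kg/h |
|---|---|---|---|
| +16 | 17.3–17.7 | 16.9–17.3 | 17.9–18.6 |
| +17 | 18.2–18.7 | 17.9–18.3 | 18.9–19.6 |

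Whether +18 is passed depends on the rise already reached, the rate and body water, and on the urine losses that the model sets to zero.

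**The case against.** Four objections have weight.

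*The primary outcome loses nothing.* A reader might infer that overcorrection events go uncounted. They do not: the outcome is confined to 48 h, and a rise caused by saline given at 48 h falls outside that window. A rise above 18 mmol/L reached later is not overcorrection as the article defines it. This stands in full.

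*The slow infusion may end at 48 h.* The general treatment section can be read that way, and the run-on figures would then fall away. This stands as a possible reading, but it leaves the slow-arm instruction at 48 h without purpose and does not deal with a bolus started at 48 h. For the same reason, a reader might infer that unmeasured late rises would fall mainly in the slow arm. The documents do not support that: they give neither the share of patients not at goal at 48 h nor its split by arm, and the asymmetry depends on the infusion running on.

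*A later sodium may exist.* A reader might infer that the effect of the last dose is never measured. The text shows only that no further protocol sample is described. Routine care may supply one. The schedule and treatment figures (Figs. 2–4) are not available, and the follow-up sentence in Study design could mean 2 days after treatment ends. The sampling sentence is also condensed, since it omits the 1-h sample listed in the arm rules. This limits confidence but does not remove the conflict: the article itself lists saline decisions at 48 h and describes nothing after them.

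*Passing +18 is not assured.* A reader might infer that any patient at +16 or +17 would exceed +18 within one further interval. The mass balance does not bear this out: at +16, neither the bolus nor 0.25 mL/kg/h reaches +18, and at +17 the result at 0.25 mL/kg/h falls on either side.

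**Conclusion.** The conflict is real and rests on the article's own text. Saline decisions are directed at 48 h in both arms, while correction, sodium sampling, fluid monitoring and the relowering check are each limited to 48 h. The 48-h action is the only one without a described sodium and relowering check after it, and the end of the slow infusion is stated inconsistently.

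The consequence is limited to safety monitoring and uniform conduct in patients not at goal with symptom relief at 48 h. On the assumptions in the working, the unmeasured rise is roughly 1.3–1.8 mmol/L after a bolus. If the infusion runs on for 6 h, it is roughly 0.9–1.3 mmol/L at 0.25 mL/kg/h and 1.9–2.7 mmol/L at 0.5 mL/kg/h. A patient already near +17 could, but need not, exceed +18 unmeasured.

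Confidence is moderate, because of the missing figures and the ambiguous follow-up wording. The point should be addressed, but it does not threaten the primary comparison.

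**What to change.** The sponsor should reconcile five sections: the general treatment guidelines, the two arm-specific rules for 24 to 48 hours, Clinical and laboratory evaluations, and Safety issues. The end of protocol 3% saline, the last protocol sodium and the overcorrection check should agree with one another and be identical in both arms. How they are aligned is a clinical choice for the sponsor, and this review does not make it.

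For patients given 3% saline at or after 48 h, record the first available sodium afterwards and its time, and report it by arm as a descriptive safety result. The 48-h window of the primary outcome stays as it is.

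The cost is a wording amendment and at most one more recorded sodium value in those patients.

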## Slow continuous correction group (Fig. 4b)

### First 24 hours

In the case of moderately severe symptoms, it is recommended to infuse 3% hypertonic saline at a rate of 0.5 mL/kg/h (25 mL/h, 3% saline for unknown body weight). In cases of severe symptoms, it is recommended to begin an infusion of 3% hypertonic saline at a rate of 1 mL/kg/h (50 mL/h, 3% saline for unknown body weight). After the initial treatment, the infusion protocol will be modified as below according to the sNa level at every sample time point (at 1, 6, 12, 18, and 24 h). If the sNa level increases to 5–9 mmol/L above the initial sNa level, accompanied by symptom relief, the 3% saline infusion should be discontinued regardless of changes in the sNa level. If the sNa level increases at a rate of under 0.5 mmol/h or 3 mmol/6 h, it is recommended to add 3% hypertonic saline infusion at a rate of 0.25 mL/kg/h to the previous infusion rate or to restart the infusion at 0.5 mL/kg/h if it was previously discontinued. If the sNa level demonstrates increases of over 0.5 mmol/h or 3 mmol/6 h, the rate of 3% hypertonic saline infusion should be maintained.

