### Study participants and measurements

All participants will be selected from among patients visiting the emergency rooms of two general hospitals in Korea (Seoul National University Bundang Hospital, Seoul National University Boramae Medical Center). Patients aged over 18 years who have moderately severe to severe symptoms and glucose-corrected sNa [25] ≤125 mmol/L on the first blood test will be screened for study participation. Moderate symptoms include nausea, headache, drowsiness, general weakness, and malaise [1, 26, 27]. Severe symptoms include vomiting, stupor, seizure, and coma (Glasgow Coma Scale (GCS)).

The following assessments will be performed during the initial emergency room encounter: (1) completion of questionnaire on medical and drug history including the use of antihypertensive medication, diuretics, nonsteroidal anti-inflammatory drugs, selective serotonin reuptake inhibitors, antiepileptic drugs, steroids, and synthyroid, (2) physical examination of all body systems, (3) measurement of height and weight, (4) blood pressure and pulse rate measurement, and (5) assessment of psychological status. Participants, who meet all of the inclusion criteria, do not require exclusion on the basis of the exclusion criteria, and provide written informed consent will be eligible for this study (Table 1).

**Table 1 Tab1:** Inclusion and exclusion criteria

Inclusion criteria	Exclusion criteria
18 years and older	Pseudo-hyponatremia (serum osmolality >275 mOsm/kg)
	Primary polydipsia (urine osmolality ≤100 mOsm/kg)
	Glucose-corrected serum sodium >125 mmol/L
	Initial arterial hypotension (SBP <90 mmHg and MAP <70 mmHg)
Glucose-corrected serum sodium ≤125 mmol/L	Anuria or urinary outlet obstruction
	Decompensated LC (LC with ascites or diuretics use or history of hepatic encephalopathy and varices)
	Bilirubin >2 mg/dL, transaminase levels >2.5 times the upper limit of normal)
Symptomatic patients	Uncontrolled diabetes mellitus (HbA1C >9%)
Moderately severe:	Women who are pregnant or breastfeeding
nausea without vomiting, drowsiness, headache, general weakness, malaise	Within the 3 months prior to randomization, history of cardiac surgery excluding PCA, acute myocardial infarction, sustained ventricular tachycardia, ventricular fibrillation, acute coronary syndrome, cerebrovascular trauma, and increased intracranial pressure
Severe:	
vomiting, stupor, seizures, coma (GCS ≤8)	

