## Rapid intermittent bolus group (Fig. 4a)

### First 24 hours

In the case of moderately severe symptoms, the use of intravenous infusion of 2 mL/kg 3% hypertonic saline over 20 min (100 mL, 3% saline for unknown body weight) is recommended. In cases of severe symptoms, it is recommended to perform intravenous infusion of 4 mL/kg 3% hypertonic saline over 40 min (200 mL, 3% saline for unknown body weight). After the initial treatment, repeated infusion of 2 mL/kg 3% hypertonic saline over 20 min at every sample time point (at 1, 6, 12, 18, and 24 h) until the observation of a sNa level increase of 5–9 mmol/L from the initial sNa and symptom relief is recommended.

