### Outcome measures

The primary outcome is the incidence of overcorrection, a surrogate marker of ODS, at any given period, defined as follows: increase in sNa level by >12 mmol/L within the first 24 h or increase in sNa level by >18 mmol/L within 48 h. The secondary outcomes will include efficacy and safety; changes in symptoms between pretreatment and 24 and 48 h after treatment with 3% hypertonic saline; time from treatment initiation to an increase in sNa ≥5 mmol/L; time from treatment initiation to the achievement of a sNa >130 mmol/L; incidence of target correction rate, defined as an achieved sNa <10 mmol/L within 24 h and a sNa <18 mmol/L within 48 h; length of hospital stay; incidence of additional treatment; incidence of ODS confirmed by the *International Classification of Disease, 10th Revision (ICD-10)* code or magnetic resonance imaging (MRI); incidence of relowering treatment; and change in GCS score between pretreatment and 24 and 48 h after 3% hypertonic saline treatment.

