### Safety issues

All adverse events related to overcorrection will be recorded and followed up during the study period or until resolution during treatment with 3% hypertonic saline. Any serious adverse events will be reported to investigators and the Ethics Committee. We will check for overcorrection at every sample time point and conduct relowering treatment as needed. Relowering treatment is performed as follows if the achieved sNa level is ≥10 mmol/L at any sample time point within the first 24 h or if the achieved sNa level is ≥18 mmol/L at any sample time point within 48 h: discontinuing ongoing active treatment; initiating infusion of 10 mL/kg of 5% dextrose over 1 h; and/or adding desmopressin 2 mcg [1].

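### On day 1, both arms let 3% saline resume after relowering in a still-symptomatic patient already back at +5 to +9 mmol/L, which can, but need not, take the rise past +12

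*Protocol article*

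**What the plan says.** All places are in the protocol article.

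- **Day-1 goal, both arms** (Physician's practical treatment guidelines): "raise the sNa level by 5–9 mmol/L from the initial sNa and to achieve symptom relief within the first 24 h".
- **Slow arm, stop** (Slow continuous correction group, First 24 hours): at a rise of 5–9 mmol/L, "accompanied by symptom relief, the 3% saline infusion should be discontinued regardless of changes in the sNa level".
- **Slow arm, restart or escalate** (same section): "If the sNa level increases at a rate of under 0.5 mmol/h or 3 mmol/6 h", the advice is to add 0.25 mL/kg/h or "to restart the infusion at 0.5 mL/kg/h if it was previously discontinued". No sodium level is attached to this trigger.
- **Bolus arm** (Rapid intermittent bolus group, First 24 hours): "repeated infusion of 2 mL/kg 3% hypertonic saline over 20 min at every sample time point", until the rise is 5–9 mmol/L and symptoms are relieved.
- **Relowering, both arms** (Safety issues): at a rise of 10 mmol/L or more at a day-1 sample, "discontinuing ongoing active treatment; initiating infusion of 10 mL/kg of 5% dextrose over 1 h; and/or adding desmopressin 2 mcg". The text does not say when 3% saline may resume.
- **Primary event, day 1** (Outcome measures): "increase in sNa level by >12 mmol/L within the first 24 h".

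Day-1 samples are at 1, 6, 12, 18 and 24 h.

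**The concern.** Slow-arm saline can have been stopped for two opposite reasons: the goal was met with relief, or sodium rose too far and had to be brought down. The restart clause does not separate them. After relowering the 6-h change is small or negative, so the trigger is met because the safeguard worked. If symptoms persist, the stop rule does not apply, and the patient goes back on saline although the sodium part of the day-1 goal is already met. The bolus rule has the same gap, because without relief it calls for another 2 mL/kg at the next sample.

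Persisting symptoms are plausible. General weakness and malaise qualify for entry, and the Discussion itself calls them usually nonspecific. At stake is patient safety: the Background puts the 24-h limit at 8–10 mmol/L, and a rise above 12 is the trial's own surrogate for osmotic demyelination. Sodium is checked every 6 h, so an overshoot between samples is found only afterwards.

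**Working it through.** The plan prints no figure on this point, so there is none to reproduce. The check applies the printed rules to a simple mixing model.

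**Inputs from the article:** bolus 2 mL/kg; restart 0.5 mL/kg/h, which is 0.5 × 6 = 3 mL/kg per 6 h; escalated rate 0.75 mL/kg/h, which is 4.5 mL/kg per 6 h; dextrose 10 mL/kg; relowering at +10 or more; primary event above +12.

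**Assumptions:** 3% saline holds 513 mmol/L sodium; body water V is 0.5–0.6 L/kg; baseline sodium is 108–125 mmol/L; infused volumes are retained; water loss is a steady drift in mmol/L/h.

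**Formulas**, with v in L/kg: saline change = v(513 − Na)/(V + v); dextrose change = −v·Na/(V + v).

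**1. Room left at +9.** There are 3 mmol/L to +12. The drift tolerated over the next 6 h is (3 − rise from saline)/6.

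| Next 6 h | Rise from saline | Drift tolerated (mmol/L/h) |
|---|---|---|
| No saline | 0 | 0.50 |
| Bolus 2 mL/kg | 1.24–1.55 | 0.24–0.29 |
| Restart 3 mL/kg | 1.85–2.32 | 0.11–0.19 |
| Escalated 4.5 mL/kg | 2.76–3.44 | below 0 to 0.04 |

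Without drift, a restart adds less than 3 mmol/L, so the rule then calls for escalation.

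**2. Loss stops after relowering at 6 h** (baseline 110, V 0.5, rise +10, no relief).
- Dextrose: −0.010 × 120/0.510 = −2.35, giving +7.65 at 12 h.
- Restart: 0.003 × (513 − 117.65)/0.513 = 2.31, giving +9.96 at 18 h. This is below 10, so there is no relowering.
- Escalation: 0.0045 × (513 − 119.96)/0.5175 = 3.42, giving +13.38 at 24 h.
- Bolus arm from the same state: +7.65, +9.19, +10.72.

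If sodium is reported in whole numbers, 9.96 reads as 10 and relowering recurs. A whole-number path that still passes +12 starts at a true +9.6 (baseline 115, V 0.5): +7.16, +9.44, +12.82, read as 7, 9 and 13.

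**3. Can the slow arm be at +10 by 6 h?** Not by saline alone. Severe regimen, 6 mL/kg: 0.006 × (513 − 108)/0.506 = 4.80 at most and 0.006 × (513 − 125)/0.606 = 3.84 at least. The moderate regimen with one escalation at 1 h gives 2.7–3.4. Reaching +9.5 needs a loss between (9.5 − 4.80)/6 = 0.8 and (9.5 − 2.7)/6 = 1.1 mmol/L/h. The paths in step 2 need that loss to stop afterwards.

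**4. Some loss continues** (severe symptoms, baseline 115, V 0.6, assumed loss 1.0 before relowering and 0.25 after). The slow arm runs +1.66, +9.93, +9.40, +12.79 at 1, 6, 12 and 18 h, from restart alone. At 18 h the bolus arm is at about +12.2, and +10.90 is reached if saline is withheld.

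**5. Sensitivity.** The grid has 972 states (rise 10–12, V 0.50–0.60, baseline 108–125), relowered at 6 h, with whole-number sodium. It shows the share of states above +12 by 24 h. These are not probabilities, and the grid does not check that each state is reachable.

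| Drift after relowering | Slow | Bolus | Saline withheld |
|---|---|---|---|
| −0.1 to +0.1 | 0–0.4% | 0% | 0% |
| 0.15 | 2.1% | 0% | 0% |
| 0.20 | 23.5% | 0% | 0% |
| 0.25 | 42.1% | 0% | 0% |
| 0.30 | 23.4% | 11.5% | 0% |
| 0.35 | 4.3% | 4.3% | 0% |
| 0.40 | 10.0% | 10.0% | 10.0% |

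From 0.40 upward relowering itself no longer holds. With unrounded sodium at drift 0.20 the shares are 94% slow and 45% bolus, and the arms are nearly equal from 0.25.

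**6. Later relowering.** Relowered at 12 h with no drift, then restarted at 18 h, no state is above +12 at 24 h.

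**The case against.** The other side has five good points.

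- The slow arm reaches +10 by 6 h only with heavy water loss, and the no-loss paths need that loss to vanish. This stands: the overshoot is conditional.
- With whole-number sodium the effect sits in a narrow band of drift that the article does not give, and desmopressin, where used, would lower that drift. This also stands, so no frequency can be claimed.
- The steps are worded as recommendations. That softens the point, but they are what staff working in shifts are told to do.
- Fig. 4b is the algorithm itself and is not shown. It may carry a limit, in which case the text should be brought into line with it.
- Treating until both level and relief are reached is the stated aim in both arms. That explains dosing before the goal, but not giving saline again just after the relowering safeguard has acted.

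A reader might infer that this is a slow-arm fault that loads the primary comparison in favour of boluses. The documents do not support that. Both rules re-dose, relowering applies equally, and the modelled gap between arms depends on rounding and on an assumed drift. A reader might also infer that following the rule makes overcorrection certain or common. Steps 3, 5 and 6 show that it does not.

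**Conclusion.** The point holds as a limited safety defect in the printed day-1 rules of both arms. After relowering, a patient back at +5 to +9 without symptom relief qualifies for more 3% saline, against the sodium goal already met. The slow arm gives the larger dose, 3 mL/kg per 6 h with possible escalation, against 2 mL/kg.

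Passing +12 is possible, not certain. In the model, with whole-number sodium, it needs mainly a residual loss of about 0.15–0.35 mmol/L/h. If the loss stops, it needs restart plus one escalation after relowering at 6 h. This rests on the assumed body water, saline content, drift and sodium rounding. How often it happens, and whether the arms differ, cannot be derived from the article. No claim is made about the planned 20% against 5%, the sample size or bias. The rules from 24 to 48 h are not at issue.

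**What to change.** Add to the day-1 text of each arm:

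*After relowering in the first 24 h, give no further 3% saline before the 24-h sample unless the rise has fallen below 5 mmol/L; then restart at 0.5 mL/kg/h without increase (slow arm) or give one 2 mL/kg bolus (bolus arm). New or worsening severe symptoms may override this and are recorded as additional treatment.*

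Severe symptoms are already defined under Study participants and measurements: "Severe symptoms include vomiting, stupor, seizure, and coma". If Fig. 4b already limits resumption, align the text with it instead.

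The cost is one sentence per arm, submitted as a modification because recruitment has begun. It needs no extra patients, samples or staff. The downside is that relowered patients with persisting non-severe symptoms may wait for more saline, up to 24 − 6 = 18 h if relowered at 6 h. In the model, at drifts of −0.1 to +0.3 mmol/L/h, none of them falls below +5 meanwhile.
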